## Abstract

**Abstract:**

The low-grade inflammation is pivotal in obesity and its comorbidities; however, the inflammatory proteins are out of target for traditional drug therapy. Omega-3 (ω3) fatty acids can modulate the downstream signaling of Toll-like receptor (TLR) and tumor necrosis factor-α receptor (TNFα) through GPR120, a G-protein-coupled receptor, a mechanism not yet elucidated in humans. This work aims to investigate if the ω3 supplementation, at a feasible level below the previously recommended level in the literature, is enough to disrupt the inflammation and endoplasmic reticulum stress (ER-stress), and also if in acute treatment (3 h) ω3 can activate the GPR120 in peripheral blood mononuclear cells (PBMC) and leukocytes from overweight non-alcoholic fatty liver disease (NAFLD) participants. The R270H variant of the *Ffar4* (GPR120 gene) will also be explored about molecular responses and blood lipid profiles. A triple-blind, prospective clinical trial will be conducted in overweight men and women, aged 19–75 years, randomized into placebo or supplemented (2.2 g of ω3 [EPA+DHA]) groups for 28 days. For sample calculation, it was considered the variation of TNFα protein and a 40% dropout rate, obtaining 22 individuals in each group. Volunteers will be recruited among patients with NAFLD diagnosis. Anthropometric parameters, food intake, physical activity, total serum lipids, complete fatty acid blood profile, and glycemia will be evaluated pre- and post-supplementation. In the PBMC and neutrophils, the protein content and gene expression of markers related to inflammation (TNFα, MCP1, IL1β, IL6, IL10, JNK, and TAK1), ER-stress (ATF1, ATF6, IRE1, XBP1, CHOP, eIF2α, eIF4, HSP), and ω3 pathway (GPR120, β-arrestin2, Tab1/2, and TAK1) will be evaluated using Western blot and RT-qPCR. Participants will be genotyped for the R270H (rs116454156) variant using the TaqMan assay. It is hypothesized that attenuation of inflammation and ER-stress signaling pathways in overweight and NAFLD participants will be achieved through ω3 supplementation through binding to the GPR120 receptor.

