#### Procedures

Figure 1A illustrates the simplified acute and chronic intervention design, and Fig. 1B illustrates the overall design and subject flow through the study. Participants may be withdrawn from the study at their request. Upon the first meeting, after being fully informed about the study and all risk factors, patients will be asked to sign the informed consent form. At this moment, the clinical questionnaire will be administrated. Instructions on a blood collection and body bioelectrical impedance test will be given. A second meeting will follow to conduct the randomization of the groups. Body composition and anthropometric profiles will be assessed, and the blood will be collected from all participants. Participants will be instructed to fill three dietary records. After randomization and 12 h of fasting, in the third meeting, the acute supplementation phase will begin. Initially, participants will perform the bioelectrical impedance test before the blood collection and before the ingestion of three capsules of placebo or three capsules of ω3 (totaling 2.2 g of ω3 [EPA–570 mg, DHA–1650 mg]), depending on the group in which they were randomized. In the meantime, because they have to wait for 3 h for the second blood collection to assess the ω3 bioavailability and ability to activate the GPR120 receptor, a 24-h recall (R24h), three dietary records will be administered and physical activity level, and anthropometric profiles will be evaluated. At the end of this meeting, an amber plastic flask protecting the capsules from light and oxygen will be provided to each participant, containing capsules available for 28 days of supplementation (3 caps/day or 2.2 g of ω3). Two days after this last meeting, the patients will report by phone call their R24h. At the last meeting and after 12 h fasting, all these assessments will be repeated.

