#### Safety, compliance monitoring, and participant retention

During follow-up, once a week, participants will report adverse events by phone, which is expected such as eructation, followed by uncomfortable gastric odor. The weekly contact will also promote participant retention to complete the study. In the case of significant adverse effects, the participant will be evaluated by the medical service from the hospital. Together with medical service, the nutritionist leader of this project will be responsible for participant stopping. Treatment compliance will be assessed by the plasma fatty acid content of patients at the beginning and the end of the experiment, which will be analyzed using a gas-chromatograph coupled to a mass spectrometer [41, 42]. See the experimental design of the interventions in Fig. 1 and the detailed schedule of assessments depicted in Table 2.

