#### Food intake

Food intake data will be obtained before and after supplementation using two R24h and three dietary records using the photographic record. Two R24h will be performed on non-consecutive days during the week and one at the weekend. The two R24h will be held on non-consecutive days, one in the third meeting and another after 2 days by phone call. The intake of each food item will be transformed into daily consumption (grams or milliliters). After, total caloric intake, nutrients (carbohydrates, proteins, fats, vitamins, and minerals) and other specific components (fibers, carotenoids, sugars, and fatty acids) will be calculated according to the nutritional composition of each source food provided priority by the Brazilian Food Composition List (TACO) [47] and by the Household Budget Survey data (IBGE, 2010) [48] when food is not found in the first one, with the help of Microsoft Excel (v. 2016) and SPSS (v. 22) software to organize and analyze the data. The values of energy consumption, nutrients, food groups according to nutritional similarity, and food groups according to the degree of industrial processing derived from the four 24hRs will be disattenuated (corrected by intra-individual variability), generating unique values for each item. This will be achieved through the PC-SIDE program (Department of Statistics, Iowa State University, Iowa, USA) developed by the National Research Council and Iowa State University [49]. Moreover, consumption values will be adjusted for energy intake by the residual method [50]. The outpatients will be instructed not to change their dietary patterns.

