#### Data treatment and statistical aspects

A steering committee will be organized for trial supervision. The process of data collection and management will be monitored by them. The committee may recommend and request the principal investigator to make some changes to the plan. To increase the security and data quality, the records will be inputted at the bank by one person and checked by another one. Data analysis will be performed according to the intention-to-treat principles [56]. The software Statistical Package for Social Sciences (SPSS), v. 22.0, will be used for data entry and analysis. Statistical analysis will be performed through descriptive analysis, with numerical variables expressed as the mean and standard deviation (SD) or median and interquartile range. All data will be subjected to the Shapiro-Wilk normality test. First, a two-way analysis of variance will be performed to check intra- and intergroup differences. Time will be added as a repeated factor, treatment as an independent factor, and the other variables (e.g., anthropometric data, food intake, blood analysis) as covariates.

The paired Student’s *t* test or Wilcoxon’s test will be used to compare the time effects. The Student’s *t* test and Mann-Whitney *U* test will be used to investigate group differences (placebo and treatment). All tests will be considered significative *P*<0.05. After trial completion, the principal investigator (PI) will be responsible for data archiving and preservation. Only investigators can access data. The PI will be responsible to terminate the trial at any moment.

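### The efficacy model leaves its covariate list open and not limited to values taken before the first capsule, and no between-arm test is named as deciding the primary outcome

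*Protocol article*

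**What the plan says.** Under Data treatment and statistical aspects, the protocol article starts with a two-way analysis of variance: time is a repeated factor, with "treatment as an independent factor, and the other variables (e.g., anthropometric data, food intake, blood analysis) as covariates". It gives no measurement time for the covariates and no closed list. Two sets of simpler tests follow. A paired Student's t or Wilcoxon "test will be used to compare the time effects", and a Student's t or Mann-Whitney U "test will be used to investigate group differences (placebo and treatment"). Beforehand, "All data will be subjected to the Shapiro-Wilk normality test". Every test uses P<0.05, and none is singled out for the primary outcome, which Study design and settings gives as a reduction in TNFα and IL6 protein in PBMCs after 28 days.

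Other sections show when the candidate covariates are measured:

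- Abstract: anthropometry, diet, lipids, "complete fatty acid blood profile, and glycemia will be evaluated pre- and post-supplementation".
- Food intake: "Food intake data will be obtained before and after supplementation using two R24h and three dietary records".
- Procedures, after the meeting at which the first three capsules are swallowed: "Two days after this last meeting, the patients will report by phone call their R24h".
- Safety, compliance monitoring, and participant retention: "Treatment compliance will be assessed by the plasma fatty acid content of patients at the beginning and the end of the experiment".

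**The concern.** A covariate measured after dosing can itself be an effect of treatment. If it lies on the causal path, adjusting for it removes part of the effect the trial is meant to estimate. If it merely shares causes with the outcome, adjusting can create a difference where none exists. Blood ω3 is the obvious candidate. It is an acute surrogate outcome, its plasma level is the compliance marker, and the hypothesis runs from ω3 through GPR120 to lower inflammation. Diet is less obvious, but one recall of the first round is taken two days into supplementation, so even the nominal baseline diet value may be partly on treatment.

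The second issue is which result counts. The primary outcome is worded as a reduction, and the plan includes a within-arm test of change. That test does not compare the arms. With no deciding test named, it could come to carry the efficacy claim.

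**Working it through.** **Inputs from the protocol article.** d = 1.15, α = 0.05, power 85%, 16 per group before dropout, 22 selected, 40% dropout (Sample size calculation); 1:1 allocation (Randomization). Two-sided testing is assumed, as sidedness is not stated. The baseline-to-day-28 correlation ρ, the shift in any post-dose covariate and the share of effect it carries are not in the document. All three are assumed and varied.

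**The plan's own figure.** At d = 1.15 and 85% power, the two-sided noncentral t gives 15 per group and the Mann-Whitney version (efficiency 0.955) gives 16. The stated 16 reproduces. An unadjusted t test has power 0.88 at 16 per group. A 40% loss from 22 leaves 22 × 0.6 = 13.2, about 13 per group, where power is 0.80.

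**Change score against ANCOVA.** With two time points, the treatment-by-time term is a t test on change.

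- SD of change = SD × √(2(1−ρ)).
- Residual SD under ANCOVA = SD × √(1−ρ²).
- Variance ratio, ANCOVA to change = (1−ρ²)/(2(1−ρ)) = (1+ρ)/2.

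For 13 per arm (24 degrees of freedom for change, 23 for ANCOVA):

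| ρ (assumed) | d on change scale | power, change | d on ANCOVA scale | power, ANCOVA |
|---|---|---|---|---|
| 0.3 | 1.15/1.183 = 0.97 | 66% | 1.15/0.954 = 1.21 | 84% |
| 0.5 | 1.15/1.000 = 1.15 | 80% | 1.15/0.866 = 1.33 | 90% |
| 0.7 | 1.15/0.775 = 1.48 | 95% | 1.15/0.714 = 1.61 | 98% |

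**A post-dose covariate on the causal path.** Simulation: 5,000 trials, 16 per arm, true effect −1.15 SD, ρ = 0.5, covariate shifted by 1.5 to 3 SD by treatment. The adjusted estimate should be −1.15 × (1 − share carried).

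- ANCOVA on the baseline outcome alone: about −1.15, power about 0.95.
- Adding a baseline covariate: about −1.15, power 0.94.
- Adding a post-dose covariate that carries half the effect: expected −0.575, simulated −0.57 to −0.58, power 0.34 (1.5 SD shift) down to 0.17 (3 SD shift).
- Adding one that carries all of it: about 0, power 0.05.

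**A post-dose covariate that shares a cause with the outcome, no true effect.** With loadings of 0.6 on the shared cause and unit covariate variance within arm, the expected bias is −(0.6 × 0.6) × shift, that is −0.36 for 1 SD and −0.72 for 2 SD. Simulated bias is −0.35 and −0.71, with type I error 0.19 and 0.40. ANCOVA on baseline alone stays at 0.05.

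**Within-arm tests.** Suppose both arms change equally by 0.5 SD of change. Each paired t test has noncentrality 0.5√n and probability p of significance. The chance that only the ω3 arm is significant is p(1−p):

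- n = 13: 0.382 × 0.618 = 0.24
- n = 16: 0.465 × 0.535 = 0.25
- n = 22: 0.609 × 0.391 = 0.24

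**The case against.** A reader might infer that the model adjusts for values measured after treatment starts. The text does not say so. All three named classes of variable are also measured at baseline, and a repeated-measures ANCOVA often takes one baseline value per participant. What stands against the plan is only that post-dose values are not excluded.

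A reader might also take the blood covariates to include the plasma fatty acid profile. That too is inference. Assessments to randomization describes a pre-randomisation panel of glucose, insulin, lipids, liver enzymes and similar tests that fits the term at least as well, and the Fig. 1 legend distinguishes biochemical from mass spectrometry analysis. For the other covariates a mediating role is weaker: participants are told to keep their diet, and weight, waist and glycemia are set aside as outcomes because supplementation is short. The attenuation figures are therefore conditional illustrations, not predictions.

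Nor do the separate tests remove or distort the effect. The between-arm t or Mann-Whitney test is a valid randomised comparison, and the treatment-by-time contrast is unbiased and does use the baseline. The 24 to 25% figure matters only if an isolated within-arm result is read as efficacy, which the article does not say will happen.

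Finally, a closed covariate list and a named primary test are often left to an analysis plan. That answers part of the point. It does not answer all of it, because the article itself states the covariate rule, in open terms and without a time limit, next to a set of tests with no stated rank.

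**Conclusion.** The point holds in limited form. The stated covariate rule permits post-dose values, and the document gives concrete reasons why that matters: measurement on both occasions, a first-round recall two days after the first capsules, and blood fatty acids that treatment is meant to change. Whether such values will enter is not known. If they did, the result could range from mild attenuation to loss of the whole effect, or to a false positive. The size depends entirely on the assumed correlations, shift and mediated share.

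The efficiency loss from the change-score contrast depends only on ρ, d = 1.15 and 13 completers per arm: 18, 10 and 3 percentage points of power at ρ = 0.3, 0.5 and 0.7. That is a reason to prefer ANCOVA, not an error in the planned contrast. The within-arm tests should not carry the conclusion, and the deciding test should be named. The normality pre-test is secondary. None of this calls for a change in sample size.

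**What to change.** For each primary outcome in Study design and settings (TNFα and IL6 protein in PBMCs), state that the deciding test is a between-arm ANCOVA of the day-28 value on arm. Limit covariates to a short closed list: the baseline value of that outcome and the variables used to form the allocation pairs described under Randomization, which should be named. All must be measured before the first capsule, so the telephone recall two days later does not qualify.

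Move post-dose blood fatty acids, day-28 blood values and on-treatment diet to a separate mediation analysis labelled exploratory. Report within-arm changes descriptively.

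The remedy works only if the immunoblot is run at baseline. The Fig. 1 legend reads as if it is added only at the end of supplementation, whereas the outcome is a reduction and time is a repeated factor. These statements must be reconciled. If a baseline immunoblot is already planned, the cost is wording alone; if not, it is one further assay round on blood taken before the first capsule.

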#### Reporting of the study results

At the end of the experimental period, the results of the biochemical and anthropometric analysis will be delivered to patients in person. Also, at the end of the study, a meeting will be planned to discuss the results individually. Absent patients will receive their summarized results by email.

## Discussion

Due to the multifaceted ω3’s ability to modulate inflammation [17, 22, 26, 28], it is not surprising to find ω3 as a panacea; however, this most widely investigated nutrient still has many unsolved questions. Several non-controlled biases and confounding factors compromise the real interpretation of ω3 actions, even those well controlled and with a high number of participants [57]. To elucidate some points related to ω3 fatty acids in human health, we designed a triple-blinded, randomized placebo-controlled intervention trial. This study has an experimental design, followed by an acute and chronic intervention in overweight and NAFLD participants, with different molecular approaches from other studies. If our strategy works, it can contribute to improving the rationale of new studies considering the solutions proposed ahead. Despite our objectives being related to w3 actions in NAFLD patients, the original studies included in our protocol were selected from cardiovascular outcomes, as this was the most investigated area of study, which contained an appropriate sample size to demonstrate and achieve statistical significance. In addition, many of these studies used similar dosages of ω3 allowing comparisons among studies.

The EPA and DHA are the most studied among ω3 species; however, this remains without any standardization related to its origin, whether from flesh fish or capsules. De Mello et al. (2009) [58] compared the effect of fatty vs lean fish intake on inflammatory markers in patients with coronary heart disease. After 8 weeks, no differences were found between the groups. The authors used six types of fatty fishes (salmon, rainbow trout, Baltic herring, tuna, whitefish, or vendace); however, the fish’s flesh fatty acid profile was not determined before the intervention, and the variation can be high among them. In fishes such as trout (*Oncorhynchus mykiss*) and salmon (*Salmo salar*), DHA is the primary ω3 prevalent type in the whole body, although fatty acids are distributed differently among their tissues. Betancor et al. (2017) [59] tested different diets for salmons and found in the control group (wild type) 6.8% of DHA in the flesh, similar to 6.2% in the flesh of rainbow trout found by Cintra et al. (2006) [60]. Despite being considered as fatty fishes, the lipid depots are out of the muscle, undisputedly the most used part in studies with humans. Betancor et al. (2017) [59] also found 25% of DHA in the liver of salmon, similar to the 27% on trout observed by Satué et al. (1996) [61]. Other conditions hard to control for are the fish gender [61] and stage of sexual maturation [62], both of which influence the fatty acid composition in all of the fish parts.

Considering these difficulties, we will adopt ω3 supplementation by capsules, even though there are several considerations to be noticed. One struggling question among the studies is the lack of oil quality monitoring in capsules [57, 63]. We previously tested some supplement brands, choosing the one with the highest similarity to the natural profile found in wild fishes from cold water. The capsules were submitted to fatty acid profile determination by a gas-chromatography coupled to a mass spectrometer, an approach considered the gold standard, and should be obligatory before interventions due to routine adulteration [63, 64]. In our study, we had access to the pharmaceutical company and traced the capsules, following the encapsulation process, since their origin (including placebo [mineral oil] capsules). The fresh capsules will also be tested a day before the beginning of the study.

Dose determination of ω3 supplement is as important as its quality. No standardized dose has been used in the literature and most of the doses used are considered very high. It is common to find well-controlled trials using ω3 associated or not with beneficial effects, under low or high doses. Considering low ω3 doses, a recently randomized placebo-controlled trial showed 12.933 participants treated with 840 mg/day of ω3 capsules (EPA 460 mg and DHA 380 mg) during 5.3 years, aiming for primary prevention (myocardial infarction, stroke, and cardiovascular mortality) [29]. The authors did not find evidence of the differences in outcomes of major cardiovascular events. On the other hand, the GISSI-Prevenzione Trial tested in 2.836 patients, a very similar ω3 dose (850 mg EPA+DHA/day [1:2]) during 3.5 years, and found a reduced rate of death, non-fatal myocardial infarction, and stroke [65]. When ω3 doses were increased, the same incongruences (major cardiovascular events) were noticed. Sixteen mild-hypertension patients taking two daily ω3 capsules (each capsule containing EPA 460 mg and DHA 380 mg), during 3 months, did not have their blood pressure altered after treatment [66], while another study followed 23 hypertensive patients using 4 g/day ω3 (each capsule containing EPA 465 mg and DHA 375 mg) during 2 months, found a very significant reduction on systolic (*P*<0.03) and diastolic (*P*<0.003) blood pressure [67]. Here, we decided to use 2.2 g of ω3 (3 capsules, 1 g each, containing EPA 190 mg and DHA 550 mg, Table 1), an intermediary ω3 dose found in relevant studies [34, 68].

Still regarding the dosage, the EPA: DHA blend is another non-standard characteristic presenting several divergent results when EPA or DHA is predominant [12, 69, 70, 71]. The difficulty in this interpretation is worsening once a recent study showed the prominent and very consistent reduction in the risk of ischemic events, cardiovascular death, and hypertriglyceridemia on 4.089 patients using 2 g of icosapent ethyl [21]. The icosapent ethyl is a highly purified ω3 from EPA (C20:5), differentiating itself because it contains two more carbons after the ester bond (C22:5). It is also important not to confound it with docosapentaenoic acid (DPA), which has the same number of carbons and double-bounds (C22:5), without natural occurrence [21].

The nutrigenomic approaches have clarified relevant differences between EPA and DHA molecules. During 10 weeks, under experimental obesity and NAFLD induced by a high-fat diet, mice supplemented with EPA or DHA exhibited distinct transcriptomic responses in the liver and muscle. In advanced NAFLD (steatohepatitis associated with fibrosis marks), the DHA reduced genes encoding liver fibrosis and immune cell recruitment, while EPA increased genes associated with cell cycle renew, without affecting the DHA targets [72]. In steatotic Zucker rats (genetic model for obesity and comorbidities) supplemented with EPA or DHA for 8 weeks, both fatty acids were useful through different signaling pathways. The EPA reduced the hepatic gluconeogenesis by inhibiting the FoxO1 transcription factor into the nucleus, while DHA reduced the fatty acid synthase (FAS) enzyme independent of FoxO1 modulation [73]. Despite distinct EPA and DHA actions, the synergy between the two appears to be most effective for global health.^73^ Here, we chose the capsule containing a natural blend similar to what is found in fishes from cold water (Table 1).

Undisputedly, the wrong placebo selection is one of the most significant limitations to pair the comparisons. Oils such as corn, sunflower, and safflower are exuberant sources of linoleic acid (ω6–C18:2), without or with insignificant ω3 (ALA–C18:3) content [47]. Despite ω6 being an essential fatty acid, its excess could induce inflammation due to high prostaglandins (PGE_2_, PGI_2_, TXA_2_) bioconversion [74, 75]. The relevance of ω6:ω3 ratio is currently questionable; however, it is still recommended to maintain this proportion around 5:1 (ω6:ω3). In western or highly industrialized societies, 20:1 is pointed as a risk to diseases with an inflammatory background [76]. Then, the use of ω6 sources as a placebo could overestimate the possible ω3 benefits [67, 77]. On the other hand, olive oil has a broad spectrum of remarkable actions due to high oleic fatty acid (C18:1–ω9) and phenolic compounds [78], underestimating the ω3 benefits. It is not an easy decision; however, molecular investigations have been contributing to reducing the probability of errors associated with fatty acid receptor homology.

The GPR40 is the receptor used by oleic fatty acid to control the intracellular inflammation cascade, similar to ω3, blocking TAK1 phosphorylation [79]; however, in humans, GPR40 has 10% of homology with GPR120 [80]. These receptors are promiscuous for both oleic and ω3 fatty acids, causing misinterpretation through cross-talk signaling [79]. After oleic cell entrance, it binds and activates the PGC1-α (PPAR-γ Co-activator 1-alpha) protein, which induces the nuclear translocation of c-MAF protein, a transcriptional factor responsible for interleukin-10 (IL10) gene transcription, the most potent anti-inflammatory interleukin [81]. Thus, through distinct manners, olive oil can mask the possible ω3 benefits [30, 34, 66]. Here, the mineral oil will be adopted because it has a low probability of interfering in the proposed outcomes or digestive emollient action at this dose [82].

GPR120 is the main ω3 receptor [17] present in several tissues [79], respondings rapidly when this molecule is present. Experimentally, 2, 3, or 4 h after administration of a single dose of a rich ω3 source (flaxseed oil), the GPR120 pathway was activated in the liver, muscle, adipose tissue [79], aorta [42], and retina [41] of obese and insulin-resistant mice. In comparison to the placebo, the ω3-treated group had the βarr2 attracted to GPR120. So far, this approach has not been tested in humans and could reflect the acute action of ω3 fatty acids, and its undescribed antiinflammatory detailed mechanism. We do not expect a reduction in inflammatory markers acutely (after 3 or 4 h); however, if GPR120 will bind to βarr2, the existence of this possibility will be firstly evidenced in humans. The choice for peripheral blood mononuclear cells (PBMCs) was supported by two studies that identified the presence of GPR120 on macrophage surface infiltered in mice aorta [42] and on Kupffer cells in the liver [83]. Raptis et al. (2014) showed the ω3 anti-inflammatory action through TAK1 inhibition, mediated by βarr2 connected to GPR120, which changed the Kupffer polarization from M1 to M2 phenotype, mitigating inflammatory stress in the liver [83].

After acute ω3 testing, subjects will be supplemented with ω3 or placebo for 4 weeks, in accordance to Jiménez-Gómez et al. (2009) [84] and Ras et al. (2014) [85], who respectively showed the reduction on IL6 mRNA content in PBMCs or reduction on hypertriglyceridemic and hypercholesterolemic patients treated with ω3 in capsules during 4 weeks. Not distant, the ER-stress response is intimately connected to inflammatory signaling, counterbalance inflammation, and apoptosis [4, 13, 42]. In hepatocytes, ER stress has a remarkable capacity to adapt to extracellular and intracellular changes to ensure that vital hepatic metabolic functions are preserved. However, in humans, numerous disturbances (e.g., hyperlipidemia, inflammation, drugs) can disturb the hepatocyte ER homeostasis contributing to hepatic lipid metabolism dysregulation and liver disease [86]. Mozzini et al. (2014) [87] described a correlation between ER-stress in PBMC and coronary artery disease. In this sense, we decided to test this correlation in NAFLD subjects and its possible reversal after ω3 supplementation.

GPR120 variation, a non-synonymous mutation (p.R270H), has been associated with obesity in humans [36]. To study such mutations/polymorphisms, large sample size is needed. Although this trial has a few numbers of participants to test for mutations, a test of the GPR120 variation will be conducted to guarantee all known aspects that may be associated with the GPR120 functioning.

Thus, considering the lack of conclusive data regarding the ω3 fatty acid in mediating the resolution of inflammation and its consequences through GPR120 in immune cells of overweight/obese and NAFLD individuals, the present study is crucial for the characterization of the signaling mechanisms and molecules that mediate these effects.

